### Procedure for unblinding if needed {17b}

Unblinding of implementation strategies assignments may occur before study completion if the Institutional Review Boards, Data Safety and Monitoring Board, or study sponsor deem that unblinding is necessary. Otherwise, unblinding of the study team members will occur upon completion of aims-specific analyses.

## Data collection and management

### Plans for assessment and collection of outcomes {18a}

#### Group reflections with CCIHP.

Each of the 12 group reflections with CCIHP (Table 4) will be recorded, transcribed, and translated. Session transcriptions and team reflection notes will be analyzed on an on-going basis to understand modifications to planned external training and support provided by CCIHP.

#### Key informant interviews (KIIs) with university leaders.

The KII guide will be drafted in English, translated into Vietnamese, piloted, revised, and back-translated into English to confirm consistency of the translation with the original intended meaning. Masters- or PhD-level social scientists at CCIHP with expertise in qualitative research and stakeholder interviews on sexual violence will conduct the interviews. Interviews will occur in the pre-implementation phase, before any educational outreach by CCIHP, and after implementation to assess views and practices related to sustainment. All interviews will occur by audio-conference call. Interviews will be recorded, professionally transcribed, and translated into English. All interviewers will keep a diary in which they will take field notes after each KII [77, 78].

#### Focus group discussions with implementation teams.

The FGD guide will be finalized in English, translated into Vietnamese, piloted, revised, and back-translated into English to confirm consistency of the translation with the original intended meaning. Similar staff at CCIHP will facilitate the FGDs with implementation teams. Discussions will be structured as 45–60-minute in-person discussions [79] held before the start of implementation training and then immediately before, during, and after implementation of GlobalConsent. FGDs will occur on-site at universities. Interviews will be recorded, professionally transcribed, and translated into English. All facilitators will take field notes after each FGD [77, 78].

#### Survey-based data collection (Aim 1 checklist; Aims 2–3).

Survey-based data from all target populations will be collected via REDCap [49], a HIPAA-compliant, web-based data system that allows for the secure collection, transfer, storage, and analysis of study data. Customized surveys will be piloted with individuals like the focal populations but at non-study universities to gauge acceptability, inform final revisions, and assess timings to minimize respondent burden (e.g., 10–15 minutes for each leader, faculty, and implementation team survey; 16 minutes for each student survey). The survey implementation protocol described, above, under “Recruitment” will be followed for at each survey wave for faculty, implementation teams, and students to maximize their participation at baseline (~80%) and retention at endline (~90%), based on prior experience surveying students in Vietnam [51].

Measurement time points will vary for each target sample, according to the project timeline (Figure 2). Leaders will be assessed twice, once before and once after implementation. Implementation teams will be assessed quantitatively at four time points: once before the start of any implementation activities, and once immediately before, during, and after implementation of GlobalConsent. Other data on the implementation will come from administrative records collected by the IT company that is responsible for delivering GlobalConsent. Faculty will complete one assessment before implementation (Year 1) and two after the planned 12-week delivery period of GlobalConsent (Years 3, 5). Three surveys will be administered to students at six-month intervals before the planned 12-week delivery period of GlobalConsent, and three six-monthly surveys will be administered at the same interval after implementation, for a total of six assessments. At each occasion, we will send to students’ smartphones an encrypted link to a REDCap survey with ~189 questions measuring two primary behavioral outcomes and seven cognitive/knowledge, attitudinal/belief, affective, and capacity-related secondary outcomes validated in the efficacy trial [33, 50, 51] (Table 6). Secondary outcomes that are included align with our theory of change (Figure 1) and showed evidence of mediation in the trial [50]. A short modification checklist of 5–10 questions will be administered at the end of each GlobalConsent program module to understand participants’ engagement and satisfaction with the module (Table 4).

#### Costing surveys (Aim 4).

Cost elements for activities involving CCIHP staff and university implementation team members are detailed in the **Appendix**. The costing items for CCIHP should be completed monthly for each CCIHP staff member involved in the GlobalConsent intervention activities. For university implementation teams, costing items should be completed monthly outside the 12-week program implementation period and weekly during the 12-week program implementation period for each team member involved. CCIHP will collect all costing forms monthly outside the 12-week program implementation period and weekly during the 12-week program implementation period, de-identify the data, and then send the forms to the health economist for cleaning and analysis.

### Plans to promote participant retention and complete follow-up {18b}

To maximize retention across occasions, we will conduct brief cognitive interviews and pilot all REDCap surveys in similar populations at other universities in Vietnam. These steps will ensure comprehension of the questions as intended, acceptability of the questions, and appropriate length to minimize participant burden. Implementation teams and the REDCap application will administer a standard protocol of internal and automated reminders to complete each survey. To clarify institutional support and to encourage participation, leaders and/or implementation team members at each participating university will send invitation letters via email prior to survey launch. After the initial survey launch, a standard protocol of follow-up communications will be implemented for all survey waves with faculty, students, and implementation team members to maximize enrollment and retention. University leaders will receive a survey link from the CCIHP study member who conducts their KII, who will confirm individually that they have completed the survey. In addition to implementing a systematic protocol for outreach, participants who complete at least part of each survey will be compensated for their time. Also, for students, we will offer options to enter a lottery to win prizes (a smartphone) after completing all pre-implementation surveys and then all post-implementation surveys.

### Data management {19}

#### Qualitative data (reflections, KIIs, FGDs, field notes for Aim 1).

KIIs and FGDs will be digitally recorded, and all recordings will be numerically labelled. Digital files will be transcribed verbatim, and all Vietnamese transcripts will be fully de-identified, with participants identified numerically or by pseudonym. De-identified Vietnamese transcripts will be translated into English. One CCIHP non-study staff member will check one random segment of each digital file against the transcription and one random segment of each transcription file against the translation to ensure accuracy and/or to make any corrections. Digital files and de-identified transcribed and translated files will be uploaded to separate folders maintained on a HIPAA-compliant, secure network drive maintained by Emory University. Each folder will be accessible only to selected study staff for the purposes of data management and/or analysis. Upon completion of the analyses or within a suitable timeframe, digital files will be destroyed to protect the confidentiality of study participants.

#### Quantitative data (Aim 1 Checklist, Aims 2–3).

The REDCap data system will be used to facilitate secure data collection, transfer, processing, and storage of quantitative data. Data-collection modules for each wave will be built in a REDCap project and self-administered on personal devices to ensure flexibility and privacy. All required fields (e.g., documentation of consent) are specified as such, and participants cannot continue with the survey until required responses are completed. Allowable response options for each question are programmed into the data system, and participants are asked to correct or to confirm any missing or out-of-range responses. Each page of the application includes a check at the bottom to ensure that participants correct or confirm any missing responses to questions on the page. The web application then transmits data entered by each participant through an encrypted network connection to a centralized database running on a secure network and infrastructure maintained by Emory University, ensuring secure electronic data movement.

Each participant is assigned a unique random number identifying him/her across study waves and REDCap projects. All identifiable data (names, contact info, etc.) and randomized ‘lower-intensity’ or ‘higher-intensity’ study arm assignment will be stored with the unique ID and accessible only to non-study staff. The Emory and Georgia State study teams will receive randomization data only after completing the main study analyses but will not have access to identifiers in the REDCap project. CCIHP and Emory staff will create and run applications for more refined range and consistency checks in the centralized database. Systematic data collection errors for each wave of data collection will be identified, resolved, and documented using the logging application in REDCap. For analyses done with external statistical software, de-identified data will be extracted and held on HIPAA-compliant, secure networks and computing workstations.

#### Cost data (Aim 4).

The completed costing forms will be checked for consistency and missing information upon receipt. If any inconsistencies or missing information are found, the forms will be returned to CCIHP or the specific university via CCIHP for correction. Once the forms are verified as complete, they will be stored with a unique university ID and personnel ID in a folder accessible only to the health economist.

### Confidentiality {27}

#### Qualitative data (reflections, KIIs, FGDs, field notes for Aim 1).

No identifying information will be recorded on the KII guide or FGD guide. All digital files will be labelled numerically. All Vietnamese transcripts will be fully de-identified, with participants identified numerically or by pseudonym. All translation files, likewise, will be fully de-identified. Digital files and fully de-identified transcription and translation files will be uploaded to separate folders on a HIPAA-compliant, secure network drive maintained by Emory University. Digital files will be accessible only to selected CCIHP staff for quality management. De-identified transcription and translation files will be accessible only to selected study staff for the purposes of analysis. Upon completion of the analyses or within a suitable timeframe, digital audio files will be destroyed to protect the confidentiality of study participants.

#### Online quantitative survey data (Aim 1 checklist, Aims 2–3).

Procedures to minimize loss of confidentiality include the encrypted entry, transfer, and storage of data collected via REDCap. Collected data also will be identified only by unique, random identification numbers with no personal identifiers. Personal identifiers, for the purposes of recontacting participants for follow-up data-collection waves, will be accessible only to non-study-team members. Confidential data will be maintained on a HIPAA-compliant, secure network drive with user-defined access to selected study team members. Data that are extracted for analysis using other statistical software will be analyzed on password protected computing systems in locked offices. Quantitative study data will be presented in aggregate form only, and participating universities will not be named in the dissemination of study findings.

#### Cost data (Aim 4).

The costing data will be presented at an aggregate level, comparing the HIS group to the LIS group. Participating universities will not be identified in the dissemination of study findings.

### Plans for collection, laboratory evaluation and storage of biological specimens for genetic or molecular analysis in this trial/future use {33}

This section is not applicable, as the study team is not collecting biological specimens.

## Statistical methods

### Statistical methods for primary and secondary outcomes {20a}

#### Qualitative data analysis (Aim 1).

Our analysis of qualitative data will be based on FRAME [36] to enable us to characterize and explain contextual facilitators and barriers to the implementation of GlobalConsent as well as planned and unplanned modifications to implementation strategies in the HIS and LIS groups. We will use rapid content analysis [80, 81] and a hybrid inductive-deductive approach [80, 81] to analyze the data. We will transfer all reflection notes, field diaries, and transcripts of KIIs and FGDs into matrices and use matrix analysis methods to examine core FRAME constructs of 1) engagement with the implementation training materials; 2) GlobalConsent delivery practices; 3) program modifications; 4) implementation strategies over time, including the nature of, timing, reasons for, and decision-makers involved in planned or unplanned implementation modifications; and 5) factors in the outer context or internal organizational context that may explain these modifications. Prior constructs and assumptions will be evaluated against the data, and new themes will be incorporated into the matrix coding scheme [82]. Matrices will systematically note the similarities, differences, and patterns in responses across participating universities and implementation-strategies groups, for a comparative synthesis of the findings [83]. Identifying these barriers, facilitators, and modifications, and their potential influence on implementation drivers and outcomes (Aim 2) and effectiveness (Aim 3) by implementation strategies group will provide insights about recommended adaptations to proposed implementation strategy bundles here as well as the time and skills needed to facilitate the implementation of GlobalConsent by operational partners at other universities.

#### Analysis of quantitative data from leaders and implementation teams (Aim 2).

One set of analyses to explore primary hypotheses for Aim 2 will examine changes over time across LIS and HIS groups in implementation drivers and outcomes among university leaders and implementation teams (Table 5). Quantitative analyses will focus on the same measures across implementation groups for comparisons within and across periods. Cronbach’s α will be estimated with the total sample (N≈78) using pre-implementation baseline survey data to confirm the internal consistency of each scale. Quantitative responses within item sets will be summed, and scores will be standardized by averaging the items in each scale. We will examine correlations of scale constructs at each time point. Comparisons between HIS and LIS groups will be conducted within each time period by target (i.e., faculty, leaders, implementation teams) to examine whether mean differences are statistically significant, at p<.05. We also will examine HIS and LIS group differences in means for implementation drivers (e.g., perceptions of leadership, collaboration, climate) and implementation outcomes (e.g., intervention acceptability, appropriateness, feasibility) at each time point. We will test for differential change over time in mixed models by testing Group x Time interactions with target responses nested within participating university.

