### Sample size {14}

Focal populations for each of these assessments include university leaders who support the GlobalConsent implementation (n=5 per university, total of 30); members of implementation teams (n≈5 per University, total≈30 members); fulltime permanent faculty at each university (estimated mean 589 per university, range 186–1038, total 3,532; based on official figures for 2021), and male student participants in GlobalConsent (estimated mean n=796 per university, range 449–1202, total=4,776 18–24 year-old, first-year undergraduate, heterosexual or bisexual men, who are attracted to women; based on official enrolment figures for 2021). We will assume 80% participation and 90% retention in each focal population.

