## Assignment of interventions: allocation

### Sequence generation {16a}

All universities in the sample are broadly matched on programs of study (health sciences) and are pair-matched on region (North, Central, South). Within matched pairs, universities will be randomized using a computer random number generator to receive ‘lower intensity’ (LIS) or ‘higher intensity’ (HIS) implementation strategies to deliver GlobalConsent to eligible undergraduate men.

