#### Statistical power for analyses of faculty data (Aim 2).

We estimated the power to test the DD models that tested for differences in the knowledge of sexual violence legality and harm between LIS and HIS groups. Using estimates for the mean score measuring the knowledge of sexual violence legality and harm in the GlobalConsent Trial [50, 51], we computed the statistical power with a linear regression model allowing a separate intercept for each university via a simulation. We used the Stata command (ipdpower, model 1, a simulations-based command that calculates power for simple linear regression modeling) to perform the simulation. With a retained sample size of ~2,543 faculty (3,532 X 0.80 participation X 0.90 retention at wave three; ~1,272 in each implementation group), a point estimate of δ of 0.12, alpha level of .05, and 5000 simulations, estimated power was .85.

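### Single-wave comparisons of HIS and LIS faculty means are judged at p<.05 with no stated allowance for university, so if run on individuals they would often be significant by chance, even before implementation

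*Protocol article*

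**What the plan says.** In the protocol article, the section on quantitative analysis of leaders and implementation teams (Aim 2) sets out two kinds of test.

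- A comparison at each wave: "Comparisons between HIS and LIS groups will be conducted within each time period by target (i.e., faculty, leaders, implementation teams"), with the purpose "to examine whether mean differences are statistically significant, at p<.05".
- A test of change: "We will test for differential change over time in mixed models by testing Group x Time interactions with target responses nested within participating university".

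Nesting appears only in the second. Under Sequence generation {16a} the unit of randomisation is the university: "Within matched pairs, universities will be randomized using a computer random number generator". There are three pairs, so three universities per arm.

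Faculty also have their own section with a DD model that includes university intercepts. Under Analytical challenges and solutions, the faculty paragraph recognises the cluster-randomised design with six universities, but ties the small-sample corrections to the DD findings. The leader and team paragraph there says those analyses must be mostly descriptive and inference confined to the samples. It does not say this of faculty. Faculty are surveyed once before implementation (Year 1) and twice after (Years 3 and 5).

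**The concern.** Norms, campus climate and acceptability are likely to be shared to some degree by people at one university. A single-wave comparison has no pre-post differencing, so any stable difference between the three HIS and the three LIS universities stays in the contrast. With several hundred lecturers per university, an individual-level standard error becomes very small while the between-university component does not shrink. Small institutional differences would then reach p<.05 with no HIS effect. A reader shown significant wave-specific faculty differences could take them for an effect of the implementation strategies. At Year 1, where no such effect can exist, the same test could suggest an imbalance of spurious certainty.

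**Working it through.** **Inputs from the protocol**
- Faculty: "estimated mean 589 per university, range 186–1038, total 3,532" (Sample size {14}). Table 1 gives 406, 1,000, 456, 186, 1,038 and 446, which sum to 3,532 (mean 588.7).
- "We will assume 80% participation and 90% retention in each focal population" (same section).
- Leaders: 5 per university. Teams: about 5 (Sample size) or about 8 (Dissemination plans).

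**Assumptions:** ICC ρ from 0.001 to 0.05; two-sided 5% test (sidedness is not stated); total variance 1; no true HIS effect; university effects independent, with no regional component.

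**The plan's own figure.** The faculty power section states "With a retained sample size of ~2,543 faculty (3,532 X 0.80 participation X 0.90 retention at wave three; ~1,272 in each implementation group"). Check: 3,532 × 0.80 × 0.90 = 2,543.04, or 1,271.5 per arm. It reproduces.

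**Formulas**, with n_j respondents in university j and N1, N0 the arm totals:
- True variance of the HIS−LIS difference: V = ρ(Σn_j²/N1² + Σn_j²/N0²) + (1−ρ)(1/N1 + 1/N0), each sum over that arm's universities.
- Variance an individual-level test uses: V_naive = s²(1/N1 + 1/N0), with s² the expected pooled within-arm variance.
- False-positive rate: 2[1 − Φ(1.96·√(V_naive/V))].

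**One allocation worked through** (universities 1, 3, 5 against 2, 4, 6; retained sizes; ρ = 0.01):
- Sizes × 0.72: 292.32, 328.32 and 747.36 give 1,368.00; 720.00, 133.92 and 321.12 give 1,175.04.
- Σn_j²/N² = 0.4017 and 0.4631.
- V = 0.01 × 0.8649 + 0.99 × 0.001582 = 0.008649 + 0.001566 = 0.010215.
- V_naive = 0.9957 × 0.001582 = 0.001575.
- V/V_naive = 6.48, so the rate is 2[1 − Φ(1.96/√6.48)] = 2[1 − Φ(0.770)] = 44%.

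**Averaged over the eight possible within-pair allocations**

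| Assumed ICC | Year 1, 80% (about 2,826) | Retained, 72% (about 2,543) |
|---|---|---|
| 0.001 | 11% | 11% |
| 0.002 | 17% | 16% |
| 0.005 | 31% | 29% |
| 0.01 | 44% | 42% |
| 0.02 | 57% | 55% |
| 0.05 | 71% | 70% |

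Simulation at the Year 1 sizes (20,000 runs per ICC) gave 11%, 31%, 43%, 56% and 72% at 0.001, 0.005, 0.01, 0.02 and 0.05.

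**Leaders and teams, same formula.** With 5 per university: 5.5% at ICC 0.01 and 7.6% at 0.05. With 8 per university: 5.9% and 9.4%.

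**University as the unit** (simulated, Year 1 faculty sizes, ICC 0 to 0.05): a t-test on six university means (4 df) rejects in 4.5–5.1% of runs, and a paired t-test on three within-pair differences (2 df) in 4.7–5.2%.

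**The case against.** The section concerned is headed for leaders and teams, opens with those two groups and uses a sample of about 78, which excludes faculty. Faculty might be there only as a loose carry-over in one parenthesis. The within-wave test is never named, nesting is acknowledged shortly afterwards, and a condensed article may leave the standard errors to an analysis plan that is not at hand. These points limit how firmly the defect can be stated. They do not remove it: the protocol itself names faculty, sets the p<.05 rule, and places nesting and the corrections elsewhere.

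The figures lean high if region explains part of the between-university variance, because the pairs are matched on region and the calculation gives no credit for that. If half of an ICC of 0.01 were regional, the relevant row would be close to 0.005, which still gives 29%.

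A reader might infer that the Aim 2 conclusion as a whole is unsafe. The documents do not support that. The Aim 2 hypothesis concerns differences over time, and it is answered by the nested Group x Time models and the DD estimate, which removes stable university differences. Nowhere does the protocol say that a single-wave difference will be read as an HIS effect. A reader might also carry the faculty rates over to leaders and teams. Their clusters are far smaller, the inflation is modest, and the protocol already restricts inference for them.

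**Conclusion.** The point holds for the secondary single-wave faculty comparisons. Under an individual-level test, the nominal 5% becomes about 11% at ICC 0.001, 29% at 0.005, 42% at 0.01 and 70% at 0.05 at the retained sample size, and slightly more at the pre-implementation wave. It rests on two assumptions: that the unnamed test ignores university, which is how the text reads, and an ICC that the protocol does not give. The direction does not depend on the ICC chosen, because the faculty clusters are large (186 to 1,038 lecturers before non-response). For leaders and teams the rate is about 5.5–6% at ICC 0.01 and 8–9% at 0.05. The main Aim 2 analyses are not affected by this point. The change is worth making because a stated decision rule would mislead if applied as written.

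**What to change.** In the Aim 2 section on leaders and implementation teams, remove the p<.05 criterion from the within-period comparisons. Report each wave's HIS and LIS means by university descriptively, and rest inference on change from the pre-implementation wave.

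If a within-period test is kept, state that it uses the six university means: a t-test with 4 df, or within-pair differences with 2 df. Adjustment for the university's baseline mean is not a general remedy, because it cannot apply to the pre-implementation wave itself.

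The cost is a change of wording and a simple university-level summary, with no change to data collection. The downside is that wave-specific tests will rarely be significant: the critical value rises from 1.96 to 2.78 (4 df) or 4.30 (2 df). That reflects the information in six randomised units.

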#### Statistical power for analyses of leader- and implementation-team data.

We estimated power to test differences in implementation drivers and outcomes of leaders and implementation teams in the HIS and LIS groups. A power analysis was conducted using G*Power [84] and entering a sample size of 78 (39 per group) with four measurement points. Based on repeated measures ANOVA for continuous variables, with alpha set a .05 and assuming a correlation between repeated measurements of .50, the sample of 78 provides excellent power (.95) to detect a small to medium difference (*d* = .33) in differences over time between LIS and HIS groups. We expect little missing data from this collection, but assuming attrition of 20% and a sample size of 62 (N = 31 per group), power still is sufficient (.95) to detect a small-to-medium effect size of *d* = .39.

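### Neither planned HIS-LIS test for leaders and implementation teams is stated to adjust for the person's own pre-implementation score, which costs precision and lets the two tests pull apart under chance baseline imbalance

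*Protocol article*

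**What the plan says.** All of this is in the Protocol article.

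- *Analysis of quantitative data from leaders and implementation teams (Aim 2)* opens by saying that the work "will examine changes over time across LIS and HIS groups in implementation drivers and outcomes among university leaders and implementation teams". It then sets out a first test: "Comparisons between HIS and LIS groups will be conducted within each time period by target (i.e., faculty, leaders, implementation teams"). The threshold for these tests is p<.05. No baseline term is given, and the pre-implementation wave is itself one of the time periods.
- The same section ends with a second test: "We will test for differential change over time in mixed models by testing Group x Time interactions with target responses nested within participating university". This model includes the baseline wave, but no adjustment for the person's own baseline score is stated.
- *Statistical power for analyses of leader- and implementation-team data* addresses differences over time between the groups, "with alpha set a .05 and assuming a correlation between repeated measurements of .50".
- *Survey-based data collection (Aim 1 checklist; Aims 2–3)* states: "Leaders will be assessed twice, once before and once after implementation". Implementation teams have four assessments, the first before any implementation activity. Table 5 lists the scales per population; implementation leadership, collaboration and climate are measured in implementation teams only.
- *Analytical challenges and solutions* describes the leader and team analyses as mainly descriptive, because the samples are small and not randomly selected.

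**The concern.** Respondents are measured before and after on the same scales, so each person's own baseline is available at no extra cost. A comparison of means within one later wave ignores it. A change contrast uses it, but with a fixed weight of 1, which is too much when the correlation is only .50. At that value both planned contrasts are less precise than one that adjusts for baseline.

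The two tests also respond to a chance baseline difference in opposite directions. If HIS respondents happen to start higher, the within-period comparison leans towards HIS and the change contrast leans against it. The section does not say which test carries the conclusion. With small samples analysed separately by target, a sizeable imbalance is likely in some of the many scales.

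The within-period rule also applies a significance test to the pre-implementation wave, where there can be no HIS effect.

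**Working it through.** **Inputs.** Correlation .50, alpha .05, N=78 with four measurements, d=.33 (or N=62, d=.39), all from the power section. Leaders: 30 in six universities (*Sample size {14}*), so 15 per arm and 5 per university. Implementation teams: about 30 (*Sample size {14}*), or six teams of about 8 (*Dissemination plans {31a}*), that is 6 x 8 = 48; so about 15 to 24 per arm. Two-sided testing is assumed.

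**1. The plan's own power figure.** Take a within-between interaction with f = d/2, noncentrality f² x N x 4/(1-.50), and degrees of freedom 3 and 3(N-2).
- N=78: .165² x 78 x 4/.50 = 16.99; power .944.
- N=62: .195² x 62 x 4/.50 = 18.86; power .963.

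Both agree with the stated .95 within two points. A between-groups reading with .33 and .39 taken as Cohen's f gives .953 and .969, so the figure does not settle which test was meant. Either way, it pools 78 people with four waves. The within-period tests are run by target, and leaders have two waves.

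**2. Variance of one HIS-LIS contrast, relative to follow-up only (independent persons, one follow-up).**

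| Correlation | Within-period | Change, 2(1-ρ) | Baseline-adjusted, 1-ρ² |
|---|---|---|---|
| .30 | 1.00 | 1.40 | .91 |
| .50 | 1.00 | 1.00 | .75 |
| .70 | 1.00 | .60 | .51 |

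Only .50 is the protocol's figure; .30 and .70 are assumptions to show the range. At .70 the adjusted contrast improves on the change contrast by .51/.60 = .85. For the mean of three post-baseline waves in teams at .50 (equal correlations), follow-up only is (1 + 2 x .50)/3 = .667, change is also .667, and adjusted is .667 - .50² = .417.

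**3. Carry-over of a chance baseline difference.** Simulation with 39 per arm and correlation .50 (20,000 runs) gave slopes of the estimate on the baseline difference of +.50 (follow-up only), -.50 (change) and 0.00 (adjusted). The variances were .0513, .0512 and .0392; .0392/.0513 = .76, close to the .75 above.

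The standard error of a baseline difference is √(2/n) SD: .37 at 15 per arm and .29 at 24. A one-standard-error imbalance therefore moves the planned estimates by about .18 SD or .14 SD, upward in one test and downward in the other.

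**4. Power per target at correlation .50 (noncentral t, person level).**
- 15 per arm, d=.80: .56 unadjusted, .68 adjusted. Difference detectable with 80% power: 1.06 against .92.
- 24 per arm, d=.50: .40 unadjusted, .50 adjusted. Detectable difference: .83 against .72.

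These values are optimistic for either method, because six universities were randomized.

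**5. Effect of clustering.** The protocol gives no intraclass correlation or stability of university means. Assume an intraclass correlation (ICC) of .01 to .10, an autocorrelation c of the university effect of 0 to .9, and total correlation .50. With m respondents per university, the correlation of university means is r = [ICC·c + (.50 - ICC·c)/m] / [ICC + (1-ICC)/m], and the best attainable ratio is 1-r². The extremes lie at ICC .10:
- m=5, c=0: r = .100/.280 = .357, ratio .87. c=.9: r = .172/.280 = .614, ratio .62.
- m=8, c=0: r = .0625/.2125 = .294, ratio .91. c=.9: r = .14125/.2125 = .665, ratio .56.
- m=13 (78/6, both targets pooled): .48 to .95.

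These take the slope that is best for university means. A single person-level slope near the within-university value b = (.50 - ICC·c)/(1-ICC) gives 1 - 2br + b². At m=8, ICC .10, c=0: b = .556 and the ratio is .98, so in that corner the gain over the within-period test almost vanishes. The change contrast there has 2(1-r) = 1.41.

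**The case against.** A reader might infer that the plan ignores baseline altogether, discards a quarter of its precision, and will report baseline imbalance as an HIS effect. The documents do not support that. The Group x Time model includes the baseline wave, and the power section addresses differences over time. A persisting group difference is not read as an HIS effect in that model, and the within-period series would show an imbalance at baseline. The quarter rests on a planning correlation and on independent persons. The protocol itself limits these analyses to mainly descriptive use, restricts inference to the sampled people, and triangulates with qualitative data.

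It can also be said that change-based analysis is a legitimate choice, used elsewhere in this protocol (difference-in-difference for faculty, comparative interrupted time series for students), and that an article may leave covariates to an analysis plan.

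All of this limits the consequence, but part of the point remains. For leaders, with two waves, Group x Time is the change contrast, and at .50 it recovers none of the precision. The within-period test is stated outright with a significance threshold, so it is not a detail left open. Seeing an imbalance at baseline does not remove it from later tests.

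One caution bears on the remedy. People are chosen purposively, and the protocol does not say whether selection preceded allocation. If it did not, a baseline difference may be real and not chance, and adjustment does not guarantee its removal.

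**Conclusion.** The point holds as a modest improvement to the analysis. As worded, neither planned HIS-LIS test for leaders and implementation teams adjusts for the person's own baseline. At the protocol's correlation of .50, with one follow-up and independent persons, both have variance 1.00 against .75 for an adjusted contrast, and they carry a chance baseline difference with opposite signs. The direction favours adjustment across the ranges examined at per-target sizes. The amount is not determined by the protocol: under the assumed clustering the ratio runs from about .56 to .91 with the best slope, and up to .98 with a single person-level slope. The relevant sizes are about 15 leaders, or about 15 to 24 team members, per arm; the leadership, collaboration and climate scales concern teams only. Because the protocol restricts these analyses to mainly descriptive use, the stake is clarity and efficiency in Aim 2; the trial's main conclusions do not depend on it.

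**What to change.** In *Analysis of quantitative data from leaders and implementation teams (Aim 2)*, for these two targets:

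- Take the wave-specific HIS-LIS contrasts from one mixed model of the post-baseline waves, with the person's own pre-implementation score as a covariate and responses nested within university. State that this model carries the inference.
- Report the baseline wave descriptively by group, without a significance test.
- Use a model with one common baseline mean only as a sensitivity analysis, since it needs participants to have been selected independently of allocation. State whether they were.

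The cost is wording; no new data are needed. The drawback is that people without a baseline score drop out of the covariate-adjusted model unless they are handled by imputation, which the protocol already plans as a sensitivity analysis, or by the common-baseline form.
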